#### Mindful attention awareness scale

The Mindful Attention Awareness Scale (MAAS) is a 15-item scale designed to assess participants’ attention and awareness of what is happening around them in the present [31]. The scale asks participants to rate statements about their mindful awareness (e.g. “I find it difficult to stay focussed on what’s happening in the present” and “I do jobs or tasks automatically, without being aware of what I'm doing”) on a 6-point Likert Scale from almost always to almost never. Higher average scores indicate higher mindful awareness. This scale will be used to determine whether watching weekly mindfulness-based podcasts will have a beneficial impact on mindful awareness.

#### App satisfaction

A study-specific, satisfaction survey has been developed for the purpose of evaluating satisfaction with the Mater mindfulness app. This survey is a 12-item questionnaire co-designed by clinicians and consumers, to assess women’s perceptions and opinions of the mindfulness intervention. Questions such as “how helpful did you find the Mater mindfulness app” and “the Mater mindfulness app improved my bonding with my baby” will be rated on 5- or 6-point Likert scales. This survey will be given to women in the intervention group.

A randomly selected portion of intervention participants (*n* = 10) will be invited to attend a focus group interview after the study. Semi-structured focus group interviews will be conducted in English, with no interpreter service available. An external facilitator who is experienced in conducting focus group interviews will be sought to facilitate these focus groups. Three primary questions will be asked during the focus group interviews, with prompt questions available to assist in guiding the interview if required:i.What did you like about the Mater mindfulness app?ii.What did you dislike about the Mater mindfulness app?iii.What would you change about the Mater mindfulness app?

#### Click analytics

Click Analytics data will be obtained through the Mater mindfulness app to measure the frequency the app is used, how long the app is used for, and which podcasts are listened to most frequently. The app will also collect ‘mood’ data at each use of the app. This will be presented on the app as a 5-point scale in the format of happy to sad faces. No other data will be collected on the app.

### Plans to promote participant retention and complete follow-up {18b}

Participants will be entered into a draw to win one of ten $100 supermarket vouchers on completion of the study. Intervention participants who agree to participate in the focus group interview to give feedback on the app will receive a $50 supermarket voucher.

### Data management {19}

All data will be collected via survey software and stored in password-protected folders on the private Mater computer network. Email addresses, for the purpose of survey distribution and matching, will be the only identifying data collected. All surveys will be de-identified and stored in a password-protected, cloud-based server in Australia, only accessible by the participating hospital. Paper records will be stored onsite in locked files, within locked cupboards. Both of these data storage sites will only be accessible by the research team. No sensitive or identifying data (including email addresses) will be collected by, or stored on, the app.

All data will be kept for a minimum of 5 years, as per NHMRC guidelines, but may be stored longer in a de-identifiable format to be used as comparative data for future projects. When data is no longer required, it will be anonymously and privately destroyed in a shredder, or deleted from the network.

### Confidentiality {27}

Confidentiality will be assured with the use of numerical pseudonyms. No identifying information will be stored with any participant information or responses. All participants will be contacted by an external research assistant. Researchers with clinical roles or other positions within the hospital will not have any direct contact with potential or consenting participants.

### Plans for collection, laboratory evaluation, and storage of biological specimens for genetic or molecular analysis in this trial/future use {33}

NA—no biological or physical specimens will be collected for this research.

## Statistical methods

### Statistical methods for primary and secondary outcomes {20a}

The primary analyses will be conducted according to the intention-to-treat principle. This means that participant data will be analysed based on the initial treatment assignment and not the treatment ultimately received. Descriptive statistics (mean/standard deviation, median/range, proportion/percentage) will be used to describe participants’ characteristics. Normality testing by visual assessment of the data will precede inferential statistical tests of continuous outcomes, such as questionnaire scores. The primary analysis of EPDS scores at 6 months postpartum will be conducted using a linear regression model to compare the intervention and control groups. This will be analysed using an independent samples *t*-test and further sensitivity analyses using analysis of covariance (ANCOVA) to determine the impact of the intervention on EPDS scores while controlling for covariates such as age and parity.

The mean change in EPDS from timepoint 1 to timepoint 4 will also be investigated. To estimate the changes within and between test groups at each timepoint, a linear mixed effects model for repeated measures will be used. The participant will be treated as a random effect, by means of the restricted maximum likelihood method (REML). The main effects of group, time, and a group-time interaction will be analysed. To determine the effect of the baby’s sex (which will only become known at timepoint two) on outcomes, the main effects of knowledge, sex, and a knowledge-sex interaction will also be measured. Additional potential covariates (age, parity, marital status, child disability, stillbirth or infant death, and previous episode of depression) will be included as fixed effects. Secondary outcomes of interest (mother-to-infant bonding, quality of life, and mindful awareness) will be analysed with the same strategy described above.

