### Criteria for discontinuing or modifying allocated interventions {11b}

Participants will be free to withdraw from the study at any time. Women who appear in distress will be flagged by the research team, removed from the study, and offered additional support. To ensure the validity of results, all data collected from participants up to the point of withdrawal will be included in the analysis, which will be conducted according to the intention-to-treat principle.

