### Outcomes {12}

Postnatal depression will be the primary outcome of the study. This will be measured using the Edinburgh Postnatal Depression Scale (EPDS). The primary outcome will be EPDS measured at 6 months postpartum. Changes in postnatal depression over time will also be assessed and will be determined by conducting the EPDS at four timepoints: 16 weeks’ gestation, 28 weeks’ gestation, 3 months postpartum, and 6 months postpartum. Secondary outcomes measured at the same timepoints will include measures of mother-infant bonding (using the *Mother-to-Infant Bonding Scale*), quality of life, and cost-effectiveness (using the *PROMIS Global-10*). The primary timepoints for these assessments will be timepoint 1 (16 weeks’ gestation) and timepoint 4 (6 months postpartum). Mindful attention (using the *Mindful Attention Awareness Scale*) will be measured at times one and four. Participant satisfaction with the app (using a bespoke survey described below) will be measured at the third timepoint (3 months postpartum), and participant adherence (measured with click analytics to detect the frequency of app use) will be examined once participants have completed the study (see Fig. 1). The study will also use click analytics to determine the frequency of app use. Demographic data and medical health information will be extracted from medical records for the purposes of inferential statistical analyses. Changes from timepoint 1 will be assessed for all health-related, repeated surveys. Measures will be analysed in aggregate form.

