### Sample size {14}

The necessary sample size was calculated using the public access software G*Power 3.1.9.7 for Windows [20]. The primary outcome of depression, as measured by the EPDS, was used to estimate the required sample size. Previous meta-analyses that found mindfulness in the perinatal period reduced depression scores with an effect size of *d* = 0.59 [21, 22]. The sample size calculation was therefore based on the estimation of a medium intervention effect (*d* = 0.50). A sample size of 128 was required to compare differences at timepoint 4, with 80% statistical power, a two-tailed significance level of 5%, and a 1:1 allocation ratio. Previous studies have reported high attrition rates of 20–45% [23, 24]. Accounting for an attrition rate of 40%, a final sample size of 214, with 107 individuals in each group, will be required.

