### Methods in analysis to handle protocol non-adherence and any statistical methods to handle missing data {20c}

All data will be analysed using an intention-to-treat study design, regardless of protocol adherence. Missing responses within partially completed surveys will be handled as per the instructions in the scoring manual for each individual survey. Where timepoint data is missing, linear mixed model analysis will retain all data, and missing data will be assumed to be missing at random.

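### The primary t-test of 6-month EPDS cannot use women without a 6-month score, about 86 of 214 at the planned attrition, and the protocol's missing-data method does not reach it

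*Protocol article*

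**What the plan says.** The Outcomes section {12} fixes the endpoint: "The primary outcome will be EPDS measured at 6 months postpartum". Statistical methods {20a} fixes the analysis: "The primary analysis of EPDS scores at 6 months postpartum will be conducted using a linear regression model". The next sentence names the independent-samples t-test and makes ANCOVA a sensitivity analysis, with age and parity as example covariates. A separate paragraph of {20a} brings in the REML mixed model for another question: "To estimate the changes within and between test groups at each timepoint, a linear mixed effects model for repeated measures will be used".

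Two other sections deal with incomplete follow-up:

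- The missing-data section {20c}: "Where timepoint data is missing, linear mixed model analysis will retain all data, and missing data will be assumed to be missing at random".
- The discontinuation section {11b}, for women who withdraw: "all data collected from participants up to the point of withdrawal will be included in the analysis". It ties this to the intention-to-treat principle.

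The Sample size section {14} expects heavy loss ("Accounting for an attrition rate of 40"%). It randomises 214 women so that 128 can be compared at timepoint 4.

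**The concern.** The protocol names a primary test, names a way of handling missing visits, and attaches the second to a different analysis. Read together, the sections give the primary result no stated protection against the 40% loss that the trial plans for. The EPDS scores that lost women gave at 16 weeks, 28 weeks or 3 months play no part in it.

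Loss related to EPDS, and differently so by arm, is plausible here. Participants know their allocation, the control is passive usual care, and only one arm is sent the app and its technical support. Section {11b} also provides for women who appear distressed to be removed from the study, so loss may follow the construct being measured. The ANCOVA covariates named as examples do not include an earlier EPDS score, so that analysis as described would not correct for it.

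**Working it through.** **1. The plan's own figures.** Inputs from {14}: d = 0.50, two-sided 5%, power 80%, 1:1 allocation, 40% attrition. The noncentral t calculation gives 63.77, so 64 per arm and 128 in all. Then 128 / (1 − 0.40) = 213.3, so 214. Both figures reproduce and are not in dispute. (The abstract's 360 is a separate discrepancy and is not used here.)

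**2. Women outside the primary test.** 214 × 0.40 = 85.6, about 86, leaving 107 × 0.60 = 64.2 per arm. Over the cited attrition range of 20% to 45%, the number left out is 214 × 0.20 = 43 to 214 × 0.45 = 96.

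**3. What each analysis uses from a woman with earlier scores but none at 6 months.**

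| Analysis in {20a} | Role | Her data |
|---|---|---|
| Regression / t-test at 6 months | Primary | None |
| ANCOVA at 6 months | Sensitivity | None |
| REML mixed model | Change over time | All observed visits |

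Only the last row delivers what {11b} and {20c} describe.

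**4. Size of a possible bias.** The protocol gives no EPDS standard deviation, between-visit correlation or dropout mechanism. The following are assumptions: SD 5; equal correlation r = 0.4 to 0.6 between visits; no true effect; 40% loss per arm; odds of loss multiplied by 1.5 to 2 per SD of 3-month EPDS in one arm, and random loss in the other.

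Let s be the shift, in SD units, of the mean 3-month score among women who stay. Then

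bias = SD × r × (s in app arm − s in control arm).

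In simulation, s is about −0.16 for an odds ratio of 1.5 and −0.25 for 2, and 0 under random loss.

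- Low end: 5 × 0.4 × 0.16 = 0.32 points.
- High end: 5 × 0.6 × 0.25 = 0.75 points.

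Direct simulation agrees, at about 0.3 to 0.75. The sign favours the app if its higher scorers leave, and goes against it if the higher scorers leave the control arm. The planned effect on this scale is 0.50 × 5 = 2.5 points, so the bias is 0.3 / 2.5 = 12% to 0.75 / 2.5 = 30% of it.

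**5. Type I error at 64 per arm.** SE = 5 × √(2/64) = 0.884.

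- Bias 0.3: 0.3 / 0.884 = 0.34; Φ(−1.62) + Φ(−2.30) = 0.063.
- Bias 0.75: 0.75 / 0.884 = 0.85; Φ(−1.11) + Φ(−2.81) = 0.136.

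**6. When there is no bias.** If both arms follow the same EPDS-dependent rule and there is no effect, the two shifts are equal and cancel. Simulation gave bias of at most 0.01 SD and rejection of about 5%. With a true effect of −0.50 SD and a stronger common rule, the t-test gave −0.45 to −0.47 SD, a modest shrinkage.

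**7. What earlier scores recover.** If the 3-month score is observed, using all earlier visits leaves about 0.02 points or less. If it is missing too, only the first two visits help. The covariance of the 3-month and 6-month scores given those visits is r − 2r²/(1 + r), which is 0.17 at r = 0.4 and 0.15 at r = 0.6. The residual bias is then about 5 × 0.15 × 0.16 = 0.12 to 5 × 0.17 × 0.25 = 0.21 points.

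**The case against.** The strongest reply is that this is only a matter of labels. Section {20a} defines intention-to-treat as analysis by assigned arm, and a t-test by assigned arm satisfies that. Section {11b} speaks of the analysis in general, and the mixed model can be read as keeping its promise. That model already estimates group differences at each timepoint, including the last. How missing 6-month scores enter the primary regression, for example by imputation, could be set out in an analysis plan that is not shown.

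Much of this stands. A reader might infer that the primary test breaches intention-to-treat; under the definition in {20a} it does not. A reader might also take the protocol to prescribe a completer analysis; it never says so. That follows from a single-visit test with no imputation named and from sizing the trial for 128 remaining out of 214.

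The reply does not remove the mismatch. The protocol does state a method for missing visits, and it is one that the named primary test cannot use. That is a conflict between stated sections, not a detail left for later. Which analysis is primary decides which result the trial reports as its answer.

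**Conclusion.** The point holds as a mismatch between {20a} on one side and {11b} and {20c} on the other. It affects about 86 of 214 women at the planned attrition. The consequence is a risk of bias of about 0.3 to 0.75 EPDS points in either direction, with type I error of about 6% to 14%, under the assumed one-arm selection.

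Two stronger readings are not supported. One is that the t-test will be biased, or biased towards the app. The documents give no arm-specific dropout mechanism, the provision on distressed women applies to both arms, and a common rule with no effect gives no bias. The other is that the mixed model removes the problem. It nearly does so when the 3-month score that drives loss is observed; about 0.1 to 0.2 points remain when that score is missing as well.

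It should still be settled before analysis, because the better-protected estimate is already planned and needs only to be named as primary.

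**What to change.** In {20a}, define the primary analysis as the group difference at timepoint 4 from the planned REML mixed model. Use all EPDS visits, time as a categorical factor, group-by-time, and baseline EPDS either as a covariate or constrained equal across arms. Keep the t-test as a supportive analysis of women with a 6-month score, and label it so. Reword {11b} and {20c} so that both refer to this primary model.

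The cost is wording and a protocol amendment; the 128 and 214 need not change. The downside is that the primary result then relies on missing at random, which {20c} already assumes. A delta-shift sensitivity analysis would show how far the result depends on that assumption, but it is optional.

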## Assignment of interventions: allocation

### Sequence generation {16a}

Participants will be randomly allocated to intervention or control using computer randomisation software, with a 1:1 allocation ratio. A permuted block randomisation technique (block size = 10) will be conducted to ensure assignment of participants will be even across the two groups. Randomisation will be stratified by the midwifery model of care.

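### The primary 6-month EPDS comparison is unadjusted: it is valid, but gives up precision and protection against chance imbalance that timepoint 1 EPDS and the stratification factor could supply

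*Protocol article*

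**What the plan says.** Outcomes {12} fixes the endpoint: "The primary outcome will be EPDS measured at 6 months postpartum". The same section has the scale given four times, the first at timepoint 1: "conducting the EPDS at four timepoints: 16 weeks’ gestation, 28 weeks’ gestation, 3 months postpartum, and 6 months postpartum". It adds: "Changes from timepoint 1 will be assessed for all health-related, repeated surveys".

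Statistical methods {20a} then states: "The primary analysis of EPDS scores at 6 months postpartum will be conducted using a linear regression model to compare the intervention and control groups". The next sentence begins "This will be analysed using an independent samples" and names the t-test. ANCOVA follows as a further sensitivity analysis, "while controlling for covariates such as age and parity".

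The same section adds two analyses beyond the primary one: the mean change in EPDS from timepoint 1 to timepoint 4, and a repeated-measures mixed model with group, time and their interaction. The mixed model carries six further named covariates, among them earlier depression. Timepoint 1 EPDS enters these two analyses as part of the response, not as a covariate.

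Sequence generation {16a} says: "Randomisation will be stratified by the midwifery model of care". That factor is named in none of the models in {20a}.

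**The concern.** A score taken at the start on the same scale usually carries information about the final score. Conditioning on it narrows the confidence interval for the same treatment difference and removes the part of that difference due to chance imbalance at the start. The stated primary analysis does neither.

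Stratified randomisation balances the groups on model of care. If that factor predicts EPDS, a test that ignores it uses a standard error larger than the design produces, so it rejects slightly too rarely.

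At stake is the efficiency and robustness of the main result, obtainable from data the trial already plans to collect.

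**Working it through.** **1. Reproduce the plan's figure.** Inputs from Sample size {14}: d = 0.50, two-sided 5%, 80% power, 1:1, attrition 40%. The noncentral t calculation for an unadjusted two-sample t-test gives 63.8, so 64 per group and 128 in total, with power 0.801 at 64 per group. Inflation: 128 / (1 − 0.40) = 213.3, so 214. Both figures match the protocol, which confirms that the sample size was built on an unadjusted comparison.

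**2. Is the primary analysis unadjusted under both names?** Yes. A linear regression with group as its only predictor is the equal-variance t-test. Naming both is loose wording without consequence.

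**3. Effect of adjusting for timepoint 1 EPDS.** Let r be the correlation between timepoint 1 and 6-month EPDS. The protocol does not give r, so a range is assumed. Residual SD = SD × √(1 − r²), hence effective d = 0.50 / √(1 − r²). The degree of freedom spent on the covariate is ignored.

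| r (assumed) | Fall in residual variance (r²) | Effective d | Power at 64 per group | Evaluable total for 80% |
|---|---|---|---|---|
| unadjusted | 0% | 0.500 | 0.801 | 128 |
| 0.3 | 9% | 0.524 | 0.837 | 118 |
| 0.4 | 16% | 0.546 | 0.865 | 108 |
| 0.5 | 25% | 0.577 | 0.900 | 98 |
| 0.6 | 36% | 0.625 | 0.939 | 84 |

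The standard error shrinks by the factor √(1 − r²), from 0.954 at r = 0.3 to 0.800 at r = 0.6. The confidence interval is therefore about 5% to 20% narrower, whatever the sample size.

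**4. Chance imbalance at timepoint 1.** With 64 per group, the standard error of the baseline difference is √(2/64) = 0.177 SD, so an imbalance of 1.96 standard errors is 0.346 SD. Unadjusted, it moves the 6-month difference by r × 0.346:
- r = 0.3: 0.104 SD, or 0.104 / 0.50 = 21% of the planned effect
- r = 0.5: 0.173 SD, or 35%
- r = 0.6: 0.208 SD, or 42%

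**5. Omitting the stratification factor.** Suppose model of care explains a share R² of EPDS variance (assumed 1% to 10%). The actual two-sided level of the unadjusted test is about 2 × [1 − Φ(1.96 / √(1 − R²))], which is 0.049 at 1% and 0.039 at 10%. Power if adjusted is about Φ(0.50 / (0.177 × √(1 − R²)) − 1.96), which is 0.81 at 1% and 0.85 at 10%. The same normal approximation gives 0.81 unadjusted. This loss is small.

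**6. Is timepoint 1 EPDS a pre-allocation measure?** The sections side by side:
- Eligibility {10}: women enter before 16 weeks.
- Informed consent {26a}: the answer used for stratification is collected with consent.
- Concealment {16b}: the number tied to a pre-defined allocation is assigned on entry.
- Trial design {8}: timepoint 1 is at 16 weeks.
- Blinding {17a}: participants know their group.

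These sections do not settle whether the first EPDS precedes allocation. Fig. 1, the schedule, was not readable in the text used here and may do so.

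**The case against.** The strongest reply is that nothing here is an error. The t-test is unbiased over randomisations, agrees with the sample size calculation and delivers the 80% power it promises. Ignoring the strata errs on the safe side for false positives. That all stands, and it limits the point to efficiency and robustness.

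Second, baseline EPDS is not ignored. The change analysis and the mixed model both use it, and earlier depression is a covariate in the latter. A reader might infer from the primary test that the plan gives no protection against baseline imbalance anywhere; the protocol does not support that. Both analyses are additional, however, and neither names model of care.

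Third, the ANCOVA covariates are given as examples, and a separate analysis plan may complete them. A reader might infer that baseline EPDS and model of care are excluded; they are only not named. Completing the list would still leave the ANCOVA a sensitivity analysis, and the protocol itself fixes the choice of primary test.

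Fourth, the gain depends on an undocumented correlation over roughly 11 months, and at r = 0.3 it is under 4 power points. This is fair, and is why a range is shown. Moreover, the Abstract gives 360 women rather than 214. With 360 × 0.60 = 216 completers the unadjusted test already has power 0.955 for d = 0.50, and the gain would then lie mainly in the interval width.

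Fifth, adjustment is not free of conditions. If the first EPDS follows allocation in unblinded women, it may already reflect allocation or early app use, and adjusting for it could bias the effect. This stands and shapes the fix.

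**Conclusion.** The point holds as an inexpensive improvement that should be made. The stated primary comparison is unadjusted and leaves out both the outcome's own first measurement and the stratification factor. For r between 0.3 and 0.6, power at 64 per group and d = 0.50 would be about 0.84 to 0.94 instead of 0.80. At r = 0.5, a 1.96-standard-error imbalance at the start would move the unadjusted result by about a third of the planned effect. The stratification factor matters less: the test is mildly conservative if the factor is prognostic. The strata are not defined in {16a}, and the services listed under Study setting {9} should not be read as the strata.

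A reader might infer that the trial is underpowered or the t-test invalid. The documents do not support either: 128 and 214 reproduce exactly, and the power lost is relative to a better analysis, not to the planned 80%. The size of the gain rests on the assumed correlation and on timepoint 1 EPDS being measured before allocation is known.

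**What to change.** In {20a}, replace the primary analysis by one linear model of 6-month EPDS on randomised group, timepoint 1 EPDS and midwifery model of care, with sparse strata pooled before the analyst is unblinded. Report the adjusted mean difference with its 95% confidence interval and keep the unadjusted t-test as supportive. Naming one model also removes the regression/t-test ambiguity.

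Add two short rules:
- State that the timepoint 1 EPDS is completed before allocation is revealed, and align {10}, {16b} and the timing of timepoint 1 with that. If it cannot be ensured, timepoint 1 EPDS should not be used as a baseline covariate.
- Fix a simple rule, blind to group, for missing timepoint 1 scores, so that women with a 6-month score are not dropped for want of a baseline.

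Apply the same approach to secondary outcomes that have a valid pre-randomisation baseline. Whether the bonding scale at 16 weeks' gestation is one needs a decision, because {18a} describes it as asking about feelings towards the child in the first few weeks.

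The cost is a few sentences. The model uses data already planned, and the sample size need not change. The small downside is having to set and follow these two rules.

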### Concealment mechanism {16b}

Allocation will be concealed until assignment occurs. Consenting participants will be assigned an identification number associated with their midwifery model of care for stratified randomisation, on entry into the study. This number will be associated with a pre-defined allocation group determined by computer-generated permuted block randomisation. Recruitment and randomisation will be conducted by separate members of the research team. As such, the investigator randomising the participants will not be aware of previous or forthcoming participant allocation.

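### The EPDS mixed model and the secondary-outcome models adjust for events that, on the natural reading, follow randomisation, and the term for knowing the baby's sex may be redundant with time

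*Protocol article*

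**What the plan says.** All the analysis text on this point is in the protocol article, Statistical methods for primary and secondary outcomes {20a}.

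- **Primary analysis:** "The primary analysis of EPDS scores at 6 months postpartum will be conducted using a linear regression model to compare the intervention and control groups". A *t*-test is named, followed by sensitivity ANCOVA "controlling for covariates such as age and parity".
- **Repeated measures:** "To estimate the changes within and between test groups at each timepoint, a linear mixed effects model for repeated measures will be used". Its core terms are given as: "The main effects of group, time, and a group-time interaction will be analysed".
- **Baby's sex:** sex is described as something "which will only become known at timepoint two", and "the main effects of knowledge, sex, and a knowledge-sex interaction will also be measured".
- **Further covariates:** "Additional potential covariates (age, parity, marital status, child disability, stillbirth or infant death, and previous episode of depression) will be included as fixed effects".
- **Other outcomes:** the secondary measures (bonding, quality of life and mindful awareness) follow the same strategy.

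On timing, Eligibility criteria {10} admits women at under 16 weeks' gestation. Concealment mechanism {16b} links each woman to a pre-defined allocation through a number assigned "on entry into the study".

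**The concern.** A model that estimates the effect of offering the app should adjust only for what was settled before allocation. Two of the listed covariates, child disability and stillbirth or infant death, read most naturally as outcomes of the current pregnancy. Only depression carries the word previous. If the app has any influence on such events, holding them fixed removes part of its effect, and the group coefficient is no longer the total effect implied by the intention-to-treat statement in the same section. The Background links poor maternal mental health to poorer infant outcomes, so on the protocol's own rationale such a pathway is possible.

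The mixed model also matters beyond its descriptive role. It is the only method that section {20c} names for missing timepoints, in a trial that plans for 40% attrition.

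The knowledge term raises a different question: whether a prespecified effect can be estimated at all, or whether the analyst will have to decide what to drop after seeing the data.

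**Working it through.** **Plan's own figure.** For d = 0.50, 80% power and two-sided 5%, the noncentral *t* calculation gives 64 per arm, 128 in total (power 0.801). With 40% attrition, 128 / 0.6 = 213.3, rounded up to 214. This agrees with Sample size {14}, and nothing below changes it.

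**1. Order of events.** Entry and allocation come before 16 weeks. The four assessments (T1 to T4) are at 16 weeks, 28 weeks, and 3 and 6 months postpartum. An index-pregnancy stillbirth, infant death or child disability is therefore not known at allocation. If coded once per woman, it would also adjust EPDS scores recorded before it happened.

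**2. Size of the adjustment problem.** The documents give no event risk and no effect of the events on EPDS, so these inputs are assumptions.

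- Number of events at a risk of 0.5% to 5%: 214 × 0.005 = 1.1 to 214 × 0.05 = 10.7 women.
- Shift in the between-group difference ≈ (effect of event on EPDS) × (between-arm difference in event risk).

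| Effect of event on EPDS (points) | Risk difference 0 | 0.01 | 0.02 | 0.05 |
|---|---|---|---|---|
| 3 | 0 | 0.03 | 0.06 | 0.15 |
| 6 | 0 | 0.06 | 0.12 | 0.30 |
| 9 | 0 | 0.09 | 0.18 | 0.45 |

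The protocol's EPDS section treats 4 points as the smallest clinically significant change. The largest entry is 0.45 / 4 = 11% of that.

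**3. Can the knowledge term be estimated?** As the text reads, knowledge is 0 at T1 and 1 at T2, T3 and T4. With categorical time,

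knowledge = I(T2) + I(T3) + I(T4) = 1 − I(T1),

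which is already in the span of the intercept and the time indicators. Rank of the fixed-effects matrix for 214 women at four timepoints:

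| Terms | Columns | Rank |
|---|---|---|
| group + time + group×time (intercept included) | 8 | 8 |
| + knowledge | 9 | 8 |
| + knowledge, sex, knowledge×sex | 11 | 10 |
| + sex, knowledge×sex (no knowledge main effect) | 10 | 10 |
| Mindful attention (T1 and T4 only), all terms | 7 | 6 |

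Exactly one term is lost. Dropping the knowledge main effect restores full rank, and every other effect stays estimable.

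**4. When the redundancy disappears.**

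- Linear time: 7 columns, rank 7. Knowledge and time correlate at 0.77, so the variance inflation is 1 / (1 − 0.60) = 2.5.
- Some women learn the sex only at birth (5%, 20% or 40% tried): 11 columns, rank 11.

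**The case against.** The strongest reply has four parts.

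*The primary result is untouched.* This stands. A reader might infer that the trial's main conclusion rests on a compromised model. The text does not support that: the 6-month regression or *t*-test names no covariates, and the sensitivity ANCOVA gives only age and parity as examples.

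*The covariates are undated.* They could mean obstetric or family history, since medical history is to be extracted from records. This is possible, and the text does not exclude it. But previous is attached to depression alone, which makes the index-pregnancy reading the more natural one. Nor does the text say whether the terms are fixed per woman or switch on when the event occurs. If history is meant, the wording still has to say so.

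*The redundancy depends on unstated choices.* This is also correct. The coding of time is not given, the knowledge and sex terms are not expressly placed in the same model as group-by-time, and the remark about timepoint two may mean the earliest time at which sex can be known. Wanting estimates at each timepoint favours categorical time, but does not settle the matter. A reader might go further and infer that the model cannot be fitted or that the treatment effect is distorted. Neither follows, because only the knowledge main effect is lost. If women learn the sex at different times, the term is estimable, but it is then a post-randomisation variable.

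*The bias is negligible.* It is probably small, and it is zero if the app does not affect these events. It would therefore be too strong to say that the randomised comparison is broken in any material way. What remains is a poorly chosen estimand with no evident gain in return.

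**Conclusion.** The point holds as a specification fault in the EPDS mixed model and in the secondary-outcome models that copy its strategy. On the natural reading, two listed covariates are post-randomisation events, and adjusting for them departs from the total intention-to-treat effect. The likely shift runs from 0 to about 0.45 EPDS points over the assumed range (event effect 3 to 9 points, risk difference 0 to 5 percentage points).

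The knowledge main effect is not estimable under three joint conditions: categorical time, one common model, and knowledge starting at T2 for every woman. Even then this does not bias the group or group-by-time effects. The primary 6-month comparison and the sample size are unaffected. The text should be corrected because the cost is trivial and the present wording leaves choices to the analyst.

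**What to change.** 1. State whether child disability and stillbirth or infant death mean history before this pregnancy or events in it.
2. In all treatment-effect models, allow only pre-randomisation covariates: age, parity, marital status and previous depression, plus history of stillbirth, infant death or child disability if history is what is meant.
3. Report index-pregnancy stillbirth, infant death and child disability descriptively by arm. Any analysis that leaves out bereaved women selects on a post-randomisation event, so label it supplementary and not a randomised comparison.
4. Take knowledge, sex and their interaction out of the treatment-effect model. Examine baby's sex in a separate exploratory model, for example sex by time.
5. If T1 EPDS is used as a covariate, first confirm that it is collected before allocation; enrolment is before 16 weeks and T1 is at 16 weeks, so this is not assured. Then model only T2 to T4 as outcomes, so that T1 is not both covariate and response.

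The cost is a change of analysis wording, made before unblinded data are seen. No data collection item and no sample-size figure changes.
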